#### Visual field test

The visual field test will be performed with the Humphrey Field Analyzer II 24-2 SITA standard strategy (Carl Zeiss Meditec). A reliable VF test has fixation losses < 20% and false-positive rate < 15%. Unreliable tests will be repeated on the same day. Visual field progression is identified when three test locations show a significant reduction in VF sensitivity greater than the test-retest variability observed on at least two (possible progression) or three (likely progression) consecutive tests, according to the EMGT criteria [21].

### Plans to promote participant retention and complete follow-up {18b}

Investigators will phone contact or send a text message to remind the participants for follow-up before each study visit. Participants who default a scheduled appointment will be contacted by the investigators to re-arrange another appointment within 2 weeks.

### Data management {19}

Clinical data will be collected and recorded by two designated technicians. Clinical examination data (e.g., IOP and axial length) will be entered on case report forms and then entered electronically. Consistency checks by another technician will be performed to ensure data entry accuracy. Optical coherence tomography RNFL/GCIPL thickness and VF sensitivity data be directly exported from the OCT and VF instruments to avoid data entry errors. All data will be stored in password-protected computers. The study will be conducted in compliance with Good Clinical Practices to ensure the rights and well-being of the participants and that the data collected are complete and verifiable from source documents. Patient files will be maintained in storage for a period of 3 years after completion of the study.

### Confidentiality {27}

No personal information will be recorded on the data sheets or electronic data files. A study code will be assigned to each participant. The document containing the information of the study code and the identity of the patient will be kept separate from the study data files and data sheets.

### Plans for collection, laboratory evaluation, and storage of biological specimens for genetic or molecular analysis in this trial/future use {33}

There are no plans for collection of biological specimens in this trial.

## Statistical methods

### Statistical methods for primary and secondary outcomes {20a}

(1) The rates of RNFL thinning (primary outcome measure) between treatment groups will be compared with linear mixed modeling after adjusting for covariates including age, axial length, glaucoma severity (baseline RNFL thickness), IOP levels during following up, OCT signal strength, multiple testing, and clustering between fellow eyes. (2) Change in VF sensitivity (measured in dB) at 1 month and the rate of change in VF sensitivity over 24 months between treatment groups will be compared with linear mixed models after adjusting for covariates. (3) Survival analysis will be performed to compare the differences in survival probabilities in (A) time from baseline to VF progression (determined by the EMGT criteria) and (B) time from baseline to progressive RNFL-GCIPL thinning (determined by TPA) between treatment groups using Cox proportional hazards models. One eye from each patient (the one selected for randomization with minimization) will be included in the analyses.

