### Outcomes {12}

The primary outcome measure is the rate of change of average RNFL thickness measured by OCT over 24 months of study follow-up. Secondary outcome measures include (1) time to VF progression (possible or likely VF progression in GPA according to the EMGT criteria [21]) over 24 months expressed in survival probability, (2) time to progressive RNFL/GCIPL thinning (defined by Trend-based Progression Analysis [17, 18, 20]) over 24 months expressed in survival probability, and (3) the rate of change of VF sensitivity over 24 months (to investigate neuroprotection) and 1 month (to investigate neuroenhancement). Change in inner retinal vessel density over the parapapillary region and the macula measured by OCT angiography over 24 months will be evaluated as an exploratory outcome measure.

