## Assignment of interventions: allocation

### Sequence generation {16a}

Patients will be randomly allocated (1:1) at the baseline visit to receive NR or placebo within 1 month of enrollment. Randomization with minimization by age (< 60 years vs ≥60 years), gender (male vs female), VF MD (<−6 dB vs ≥ −6 dB), spherical equivalent (<−6.0D vs ≥ −6.0D), mean IOP measurement over the past 3 years (≤21 mmHg vs > 21 mmHg), and number of glaucoma medications (0, 1, 2, 3, or ≥ 4) will be performed using an open-source computer program MinimPy [24]. A random element was introduced in the minimization procedure (i.e., weighted randomization of 0.8) to make the randomization more unpredictable [25]. If both eyes are eligible for inclusion, the one with smaller VF MD will be selected for randomization with minimization.

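### The covariates named for the primary RNFL slope model share only age with the six minimisation factors, so the balance is not fully credited: a mildly conservative test and a small loss of power

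*Protocol article*

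**What the plan says.** Protocol article, Sequence generation {16a}: "Randomization with minimization by age (< 60 years vs ≥60 years), gender (male vs female), VF MD" are the first three factors, the last of them split at −6 dB. Three more follow: refraction as spherical equivalent, split at −6.0 D; average IOP in the 3 years before entry, split at 21 mmHg; and the count of glaucoma drugs in five levels. The random element is given as "weighted randomization of 0.8".

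Outcomes {12}: "The primary outcome measure is the rate of change of average RNFL thickness measured by OCT over 24 months of study follow-up".

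Statistical methods {20a}: the primary rates "will be compared with linear mixed modeling after adjusting for covariates including age, axial length, glaucoma severity (baseline RNFL thickness"). The list then goes on to follow-up IOP and the signal strength of the scan. The same list also names multiple testing and fellow-eye clustering, which are not patient covariates. The VF models are said to be adjusted, but their covariates are not named. No covariates are mentioned for the Cox models.

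**The concern.** When allocation is balanced on factors that predict the outcome, the treatment estimate becomes more precise. A model that leaves those factors out still counts their contribution as unexplained variation. Its standard error is then too large for the design, the test rejects less often than its nominal level, and some power is given up.

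The form of adjustment matters because the outcome is a slope. A baseline variable entered only as a main effect shifts a patient's level at every visit equally. It does not explain differences in rate, so it does not adjust the treatment-by-time contrast.

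At stake is a modest amount of power that could be had from data already needed for allocation.

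**Working it through.** **1. The two lists side by side**

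| Minimisation factor ({16a}) | Counterpart named for the primary model ({20a}) |
|---|---|
| Age | Age |
| Gender | None |
| VF MD | Baseline RNFL thickness (related) |
| Spherical equivalent | Axial length (related) |
| 3-year mean IOP before entry | IOP during follow-up (related, but post-randomisation) |
| Number of medications | None |

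One factor of six is shared, three have a partial proxy and two have nothing.

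**2. The plan's own sample size**

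Inputs from Sample size {14}: difference 0.7 μm/year, slope variance 1.39, residual variance 3.83, power 80%, alpha 5% (taken as two-sided, which reproduces the figure). The schedule gives 3 scans at months 0, 1 and 24, and one every 2 months from month 4 to month 22, so 19 scans.

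- Σ(t − t̄)² = (3751 − 205²/19)/144 = 10.689 years².
- Variance of one patient's slope = 1.39 + 3.83/10.689 = 1.748.
- n per arm = 2 × (1.960 + 0.842)² × 1.748/0.7² = 56.0. The plan states 56.
- Total = 112/0.90 = 124.4, rounded up to 125, as stated.
- Power at 56 per arm = 80.0%.

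No covariate enters this calculation, so the stated size does not depend on the covariate list. Slope variance makes up 1.39/1.748 = 80% of the per-patient variance, and intercept variance does not appear.

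**3. Effect of the unnamed factors, by formula**

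Let R² be the share of slope variance that the unnamed factors explain beyond the listed covariates. The documents give no value, so it is an assumption. With V = 1.748 and V(R²) = 1.39 × (1 − R²) + 0.358:

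- adjusted power = Φ(0.7/√(2V(R²)/56) − 1.96)
- power with the factors balanced but omitted = Φ((0.7 − 1.96 × √(2V/56))/√(2V(R²)/56))
- type I error when omitted = 2 × [1 − Φ(1.96 × √(V/V(R²)))]

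| R² | V(R²) | Type I, omitted | Power, omitted | Power, adjusted |
|---|---|---|---|---|
| 0 | 1.748 | 5.0% | 80.0% | 80.0% |
| 0.10 | 1.609 | 4.1% | 81.0% | 83.1% |
| 0.20 | 1.470 | 3.3% | 82.1% | 86.3% |
| 0.30 | 1.331 | 2.5% | 83.3% | 89.4% |

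This assumes perfect balance.

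**4. The same by simulated minimisation**

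Settings: six factors, weight 0.8, 112 patients, age always in the model, and R² split equally over the other five factors, with independent and evenly spread levels. There were 6,000 null trials and 4,000 trials with a 0.7 μm/year difference per row. Monte Carlo standard errors are about √(0.05 × 0.95/6000) = 0.3 points for type I error and √(0.8 × 0.2/4000) = 0.6 points for power. Both analyses were run on the same simulated trials.

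| R² | Type I, omitted / adjusted | Power, omitted / adjusted |
|---|---|---|
| 0 | 4.8% / 4.9% | 79.4% / 79.1% |
| 0.10 | 4.5% / 5.1% | 80.2% / 82.2% |
| 0.20 | 3.6% / 5.3% | 80.8% / 85.4% |
| 0.30 | 2.7% / 4.8% | 82.1% / 89.0% |

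Power forgone is about 2, 5 and 7 points at R² of 0.10, 0.20 and 0.30. At R² = 0, five unnecessary covariates cost about 0.3 points.

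**5. Main effect only**

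With complete data on a common schedule, the treatment-by-time contrast is the difference in mean patient slopes. A term that is constant over time drops out of every patient's slope. In 360 simulated trials with 62 per arm, adding baseline RNFL as a main effect left the standard error at 0.238 with and without it. The formula gives √(2 × 1.748/62) = 0.237.

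**The case against.** The strongest reply is that the article is condensed and its covariate list is open: it is introduced by *including*, so no factor is expressly excluded. That is true, but the article does commit to named covariates, and it leaves optional the factors that the design chose to balance.

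Several stronger readings are tempting, and the documents do not support them:

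- *The balance is wasted.* Age is in the model, three proxies carry part of the information, and balance makes the estimate more precise even when the model's standard error does not show it.
- *The covariates are main effects only.* The article states no functional form. It neither requires nor rules out interactions with time, so this is an ambiguity to close and not an error.
- *The Cox models are unadjusted.* The article is silent, and that detail can properly sit in the analysis plan.
- *Adjustment lifts power from 80% to 83% or 86%.* If the factors matter and are balanced, the model without them already has somewhat more than 80% power. The fair comparison gives about 2 to 5 points.
- *The trial is underpowered or type I error is inflated.* Neither follows. The sample size reproduces without covariates, and the omission errs on the conservative side.

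It also stands that R² has no source in the documents. Given the proxies already listed, it could be close to zero.

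**Conclusion.** The point holds as a mismatch between the allocation and the primary analysis, with a modest consequence. To the extent that the unnamed factors predict the rate of RNFL thinning, the test is mildly conservative and some power is forgone: about 2 to 5 points, with type I error of about 4.5% to 3.6%, if they explain 10% to 20% of slope variance beyond the listed covariates. If they explain about 0%, nothing is lost. These sizes rest on an assumed R² and on the plan's own variance figures. The planned 80% power, the 56 per arm and the 5% limit on type I error all stand. This is a cheap improvement worth making, not a flaw that threatens the conclusion.

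**What to change.** In Statistical methods {20a}, name the minimisation factors as covariates in the RNFL and VF mixed models:

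- age, VF MD and 3-year mean IOP as continuous values, and gender;
- number of medications as a linear score;
- axial length or spherical equivalent, but not both;
- pre-randomisation 3-year mean IOP in place of follow-up IOP for the primary estimate.

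State that each of these baseline factors enters the slope models together with its interaction with time. Baseline RNFL thickness can stay: its overlap with VF MD blurs those two coefficients, and the treatment contrast is little affected. Covariates for the Cox models may be left to the analysis plan.

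The cost is a change of wording and a few degrees of freedom, about 0.3 points of power in the simulation if the factors turn out to be irrelevant. Allocation already requires these variables, so no extra patients or visits are needed. The wording should be settled before unblinding, so that the choice of covariates cannot depend on the results.

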### Interim analyses {21b}

Interim analyses will be performed by a statistician after data collection at (A) 4 months and (B) 12 months. The rates of change of VF sensitivity and RNFL thickness will be compared between treatment groups. The participants and investigators will remain masked to the study groups. The trial steering committee will stop the trial if the rate of VF sensitivity decline and the rate of RNFL thinning were significantly worse in the NR-treated group than the placebo-treated group.

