### Sample size {14}

In our pilot study following 236 glaucoma patients every 4 months for ≥3 years, the mean rate of RNFL thinning was 1.2 μm/year (*P* < 0.001) for eyes with evidence of progressive RNFL thinning detected by TPA; the slope variance was 1.39 (μm/year)^2^ and the residual variance was 3.83 μm^2^ [20]. We aim to detect a difference of at least 0.7 μm/year in the rate of RNFL thinning between treatment groups, given that the mean rate of age-related RNFL thinning has been reported to be approximately 0.5 μm/year [22]. Taking reference from the method of sample size calculation for linear mixed modeling to compare the rates of change of a parameter of interest between two treatment groups described by Ard and Edland [23], 56 patients per study arm are needed for serial RNFL thickness measurements at baseline, 1 month, 4 months, and then every 2 months for 24 months (3 separate measurements will be collected at the baseline, 1-month, and 24-month follow-up visits) with a power of 80% and an alpha of 5%. Assuming a default rate of 10% during study follow-up, a total of 125 patients will be recruited.

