## Oversight and monitoring

### Composition of the coordinating center and trial steering committee {5d}

The coordinating center is located at the University of Hong Kong Glaucoma and Optic Nerve Diagnostic Center. The trial steering committee is directed by the principal investigator and includes two independent researchers and one statistician, who are not part of the same institution as any of the members of the study team. The trial steering committee is responsible to ensure the protocol is implemented as planned, review study progress on a regular basis, and uphold good clinical practice at all times. The coinvestigators, research assistants, and technicians of the trial will be responsible for all aspects of the logistics and organization of the trial.

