### Composition of the data monitoring committee, its role, and reporting structure {21a}

An independent data monitoring committee comprises two independent experts in statistics, who are not part of the same institution as any of the members of the study team. They will be responsible to inspect clinical data collected during the study period, review interim analysis, and report back to the investigators if any action is required.

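### The interim harm decision sits with a committee directed by the masked principal investigator, and the rule is nearly inert at 4 months if data are cut there

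*Protocol article*

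**What the plan says.** Three sections of the protocol article bear on this.

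- **Interim analyses {21b}.** A statistician compares the VF and RNFL slopes between arms at 4 and 12 months. "The participants and investigators will remain masked to the study groups". The decision follows: "The trial steering committee will stop the trial if the rate of VF sensitivity decline and the rate of RNFL thinning were significantly worse" on NR than on placebo. The two slopes are joined by *and*.
- **Composition of the coordinating center and trial steering committee {5d}.** "The trial steering committee is directed by the principal investigator". Its other members are two independent researchers and a statistician from outside the study team's institutions.
- **Composition of the data monitoring committee {21a}.** Two independent statistical experts inspect the clinical data, "review interim analysis, and report back to the investigators if any action is required". No stopping decision is assigned to them.

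Under Implementation {16c} the principal investigator enrols participants. Under Adverse event reporting and harms {22} the investigators and the steering committee decide whether an event is related to the study drug.

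**The concern.** To apply the rule, a body must know which arm is NR, which way each slope difference points, and whether each is significant. Slopes under masked arm codes would not be enough. The body named is directed by an investigator who is meant to stay masked. If that person learns the comparison at month 4, causality judgements over as much as 20 further months of a patient's follow-up are made with that knowledge.

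The second issue is whether the rule protects patients. It needs two significant slopes, and the first look comes when a slope can rest on only 4 months of data. A safeguard that cannot respond to plausible harm may give false reassurance.

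**Working it through.** **Who decides and who sees.** Set side by side, {21b} masks the investigators and gives the steering committee the decision, {5d} puts the principal investigator at the head of that committee, and {21a} has the DMC review and report to the investigators. No section restricts results by arm to named people.

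**Inputs (Sample size {14}).** "the slope variance was 1.39 (μm/year)^2^ and the residual variance was 3.83 μm^2"; "We aim to detect a difference of at least 0.7 μm/year in the rate of RNFL thinning between treatment groups"; "with a power of 80% and an alpha of 5"%; "3 separate measurements will be collected at the baseline, 1-month, and 24-month follow-up visits", with single scans at 4, 6, …, 22 months. The stated size is 56 per arm, or 125 in total after 10% default.

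**Formulas.** Variance of one patient's slope: V = 1.39 + 3.83/Sxx, where Sxx is the sum of squared deviations of scan times in years. SE of the difference = √(2V/n). Probability of flagging a true worsening d = Φ(d/SE − 1.96).

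**Reproducing the plan's figure.** Over 24 months there are 19 scans, with Sxx = (3751 − 205²/19)/144 = 10.689 and V = 1.748. Then n = 2(1.960 + 0.842)² × 1.748/0.7² = 56.0, and power at 56 is 79.99%. The model matches the plan.

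**The looks, each patient's data cut at the named month.**

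- Month 4: 7 scans (three at 0, three at 1, one at 4). The mean time is 1 month, so Sxx = (3×1 + 0 + 9)/144 = 0.0833 and V = 47.35.
- Month 12: 11 scans. Sxx = (363 − 43²/11)/144 = 1.354 and V = 4.220.

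| Look | Share of final information | SE (56 / 62 per arm) | Flag +0.7 | Flag +1.2 |
|---|---|---|---|---|
| Month 4 | 1.748/47.35 = 3.7% | 1.30 / 1.24 | 8% / 8% | 15% / 16% |
| Month 12 | 1.748/4.220 = 41% | 0.388 / 0.369 | 44% / 48% | 87% / 90% |

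The smallest significant worsening at month 4 is 1.96 × SE = 2.55 or 2.42 μm/year, about twice the whole 1.2 μm/year pilot rate. These are RNFL-only figures at two-sided 5%. The article gives no interim level. One-sided 5% would give 13% to 14% (month 4) and 56% to 60% (month 12) for +0.7.

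**If the first look uses all accrued data.** Assume uniform accrual over the 12-month recruitment period and a look when the last patient reaches month 4. Last completed visits are then 4, 6, 8, 10, 12 and 14 months, one sixth of patients each, with V = 47.35, 17.67, 9.27, 5.88, 4.22 and 3.30. The mean of 1/V is 0.1492. SE = √(2/(56 × 0.1492)) = 0.489, or √((1/62 + 1/63)/0.1492) = 0.463 with all 125 patients. The flagging probability is 30% to 33% for +0.7 and 69% to 74% for +1.2.

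**Adding the VF condition.** No VF variance or effect is given, so VF power has to be assumed. For +0.7 on RNFL, 56 per arm, data cut at each look and correlation 0 to 0.5 between the two test statistics:

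- VF power 10% to 50%: joint probability 1% to 7% at month 4 and 4% to 30% at month 12.
- VF power 80%: 35% to 40% at month 12.

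**The case against.** A workable reading exists. The statistician runs the comparison, the DMC reviews it and speaks only if action is needed, and the steering committee acts on that advice without seeing results by arm. Stopping on a DMC recommendation is ordinary, and the steering committee has independent members. A fuller protocol or charter may set out the information flow. This stands to the extent that the sections do not contradict each other outright, and nothing says the principal investigator receives results by arm. It does not remove the risk, because the article itself names the steering committee as the body applying the rule and assigns the DMC no such decision.

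A reader might infer that VF testing would be contaminated. The documents show no such route: the technicians are masked, outcome assessors are blinded, and VF and OCT data are exported directly from the instruments. Causality judgement is the documented exposure.

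A reader might also infer that the rule can hardly trigger at all, or would miss large harm. That fails at month 12, which holds about 41% of final RNFL information and where RNFL alone flags +1.2 with 87% to 90% probability. Even the month-4 result depends on cutting each patient's data there.

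Finally, requiring both slopes guards against stopping on noise, and individual exit criteria, adverse-event checks and DMC inspection of data also operate. All true. The two-slope condition is a defensible trade-off, not an error.

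**Conclusion.** The concern holds in limited form. The three sections leave an avoidable risk of unmasking the principal investigator and need to be reconciled. Unmasking is a risk here, not something the plan provides for.

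The harm rule is nearly inert at the first look if data are cut at 4 months, and limited for a harm of the design size if all accrued data are used. At 12 months it is weak for a harm of the design size but, on RNFL alone, not for a doubling of thinning. All RNFL figures are upper limits for the two-slope rule, whose true power cannot be fixed without VF inputs. They assume the protocol's variances, two-sided 5% at each look, no covariate adjustment and no missing visits. The 12-month figures also assume a cut at 12 months; later accrued data would raise them.

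**What to change.** Reconcile {21b}, {5d} and {21a} so that they state:

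1. Only the interim statistician and the existing independent DMC see results by arm.
2. The DMC applies the harm rule.
3. The steering committee and the investigators receive only a recommendation to continue or stop.

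Also state whether each look uses all accrued data or cuts each patient at the named visit. Do not rely on the 4-month slope comparison as a safeguard; have the DMC review safety endpoints and adverse events by arm at that look.

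The form of the 12-month boundary is for the sponsor and the DMC to choose. For example, a boundary on either outcome at one-sided 1% each would carry at most about a 2% false harm signal. It would lower the RNFL limb for +0.7 from 44%–48% to about 30%–33%, but would no longer need VF to agree.

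The cost is protocol and charter wording, using bodies that already exist. No efficacy alpha is spent.
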